#### Qualitative analysis

The data will be analyzed using the content analysis method proposed by Bardin [88], specifically the thematic content analysis, which allows the organization of textual content, to create categorizations and facilitate inferences and perceive patterns. Content analysis can be defined as a set of methodological instruments, in constant improvement, which lend themselves to analyzing different sources of content (verbal or non-verbal). This thematic analysis aims to discover the nuclei of meaning that constitute communication and whose presence may have some meaning for the chosen analytical objective, in addition to seeking answers to questions. With this technique, one can walk towards the discovery of what is hidden in the manifest contents, going beyond the appearances of what is being analyzed. Content analysis will be organized into three phases: (1) Pre-analysis (when you will listen to the audio and visualize the notes); (2) Exploration of the material (interview transcription); (3) Treatment of results: inference and interpretation (in this phase, the material will be read and re-read, in order to highlight relevant points and use a tool for visualization and tabulation of the most recurrent subjects in all the analyzed interviews). In this perspective, the next stage of the analysis will be the categorization of responses, according to a detailed and exhaustive study of the participants’ statements, which will enable the construction of categories to be discussed and analyzed.

The person responsible for analyzing the data will not know which group is control or intervention. In addition, data analysis will not be performed by a researcher from the study group.

### Interim analyses {21b}

If necessary, there will be intermediate reviews and termination guidelines. The responsible researcher will have access to this information and will make the decision.

### Methods for additional analyses (e.g., subgroup analyses) {20b}

There will be no further analysis. The analyses carried out are described in the study.

### Methods in analysis to handle protocol non-adherence and any statistical methods to handle missing data {20c}

In case of non-adherence of the participants, the intention-to-treat method will be used. The intent-to-treat method is a statistical approach used in clinical trials and experimental studies to analyze outcomes regardless of compliance with the original protocol. The principle of the intention-to-treat method is that participants should be analyzed according to the group to which they were initially assigned, regardless of whether or not they followed the treatment as planned.

### Plans to give access to the full protocol, participant-level data, and statistical code {31c}

The data will be made available to readers, if requested by email.

## Oversight and monitoring

### Composition of the coordinating center and trial steering committee {5d}

#### Coordination Center

Study leaders will be available at any time to answer questions from participants.All will be available in the research lab and online communication networks.The group of advisors will be two (2) physiotherapist researchers responsible for the general direction of the study. One (1) rheumatologist responsible for the clinical aspects of the participants and one (1) person with fibromyalgia. All participants in this coordination group will be attentive to the event of the study. Weekly support may be requested. In addition, this group may meet to discuss the progress of the study every 15 days.

#### Trial steering committee

A participant support committee with three members: one (1) physiotherapist, one (1) rheumatologist and one (1) patient with fibromyalgia. All three members of this committee have the role of managing and supervising all the steps of the study, as well as solutions for any problems that may exist.

#### Stakeholder and Public Involvement Group (SPIG)

There will not be, as this study does not present commercial stakeholders, as well as the public. This is a research without conflict of interest.

### Composition of the data monitoring committee, its role and reporting structure {21a}

The Data Monitoring Committee will be composed of experts outside the study. Therefore, the following professionals will be part of it: 2 physiotherapists (analyzing data collection, ethical aspects with data management and data storage), 1 physician specialized in rheumatology (responsible for monitoring the applied instruments and how to use the data, as well as, care with the data of the participants) and a statistician (responsible for the storage and quality of the data). If it is necessary to write a report, these specialists will be responsible for this function and will send it to the researchers responsible for the study. In addition, all members of the Data Monitoring Committee are independent experts and have no connection with competing interests or sponsors/financiers.

### Adverse event reporting and harms {22}

#### Notification of adverse events (AEs)

The minor adverse events that can happen are falls during physical exercise. If any happens, it will be immediately communicated and verified by the Data Monitoring Committee.

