Regarding the physical exercises that should be included in the treatment of individuals with fibromyalgia [10], a recent review on physical exercises for fibromyalgia published in the Cochrane Database of Systematic Review [40] highlights that no evidence was found of improvement in pain superior to that of the study by Assumpção et al. [41], where improvement was at 30%. In this sense, we chose to use the aforementioned protocol [41], which meets the guidelines of the European Alliance of Associations for Rheumatology [10], highlighting that for non-pharmacological interventions in the management of fibromyalgia, patient education is indicated, in association with physical exercise. Assumpção et al. [41] suggest the inclusion of both approaches in exercise therapy programs for fibromyalgia in clinical practice.

Exercise sessions should be performed online with an approximate duration of 40 min each, once a week, for flexibility and low-intensity strengthening exercises [41]. Participants will be instructed to position themselves correctly to perform the exercises and, at all times, correct body alignment awareness will be emphasized [41]. The physical exercises will be interspersed: muscle stretching 1 week, and muscle strengthening the other. Participants will be tended to online as a group and under the guidance of a physiotherapist. Figure 2 presents the structure of the physical exercise program, based on Assumpção et al. [41] and the American College of Sports Medicine (ACSM) [42].

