**Fig. 2 Fig2:**
[figure not shown]
“Amigos de Fibro (Fibro Friends)” physical exercise program

It is important to note that we considered the new version of guidelines on physical activity created by the World Health Organization in 2020 [43]. In this sense, the current guidelines recommend that all adults and elderly individuals with chronic conditions should perform at least 150 to 300 min of moderate-intensity aerial physical activity; or at least 75 to 150 min of vigorous-intensity aerial physical activity; or an equivalent combination of moderate-intensity and vigorous-intensity physical activities throughout the week for substantial health benefits [43]. So, considering that fibromyalgia is a chronic pain syndrome that has an important negative impact on the quality of life of patients, all participants will be instructed on the frequency and time of physical activities that should be performed per week and encouraged to perform them at home, in addition to what was proposed in the web-based program, to ensure the benefits of regular physical activity [43].

The “Amigos de Fibro (Fibro Friends)” program will be conducted by the invited professionals, according to the themes of each meeting that were developed in the first phase of the study, based on the National Health Promotion Policy [44], and is presented in Fig. 3. The development of “Amigos de Fibro (Fibro Friends)” was published and showed a good level of agreement among evaluators [45].

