#### Control group

Participants in the CG will receive an educational self-care e-book that was prepared by the authors themselves and that will address the same information that was defined in the construction of “Amigos de Fibro (Fibro Friends)”. The order of the themes of the e-book will be the same as presented in the experimental group. The e-book will have weekly chapters, meaning each week you should read a chapter with the information and note the start and end date of the reading. The choice of weekly chapters is for the CG to finish participating in the study at the same time as the experimental group. Moreover, once a week, the responsible physiotherapist will call each participant of this group to ask how the reading is going and to remind them to carry it through weekly.

The final version of the e-book is comprised of 90 pages, with the title “Amigos de Fibro (Fibro Friends)”: Promoting Health in Fibromyalgia”. The e-book was created using the Canva software, a graphic design platform that allows users to create different types of visual content. In addition, it features graphic illustrations taken from Envato Elements, a subscription platform for graphic design items. The material was divided into 10 blocks with the following themes: getting to know fibromyalgia (chapter 1), health promotion and care (chapter 2), family and work (chapter 3), body practices and physical activities (chapter 4), healthy and adequate nutrition (chapter 5), health and well-being (chapter 6), pharmacological approach (chapter 7), integrative and complementary practices (chapter 8), occupational performance (chapter 9), and sleep quality (chapter 10).

The educational content refers to self-care measures that promote the health and quality of life of individuals with fibromyalgia. In order to enrich the content, improve readability and general reader captivation of the e-book, and offer the target audience the opportunity to delve deeper into the topic, references, and links were added to the end of the material, which give access to the entirety of articles, books, theses, and websites that also support the material’s theoretical framework. The e-book has already been validated and published and showed a good level of agreement among evaluators [31]. The final version of the e-book is available at http://www.amigosdefibro.com.br.

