#### Reporting of serious adverse events (SAEs)

Evidence suggests that SAEs are not expected, however, if any serious adverse effects occur, they will be immediately reported and analyzed by the Data Monitoring Committee.

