#### Notification of intervention harm

In some situations, research may have unplanned or unforeseen harm or consequences, which may result in collateral damage or unwanted effects. If any of these happen, they will be immediately communicated and verified by the Data Monitoring Committee.

Participants will have an online communication channel (telephone and email) to fill out a form highlighting adverse effects and harm. A secretary will forward the message to the Data Monitoring Committee.

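### The only harms-capture route described is an unsolicited participant form, with no scheduled harms question in either arm and falls called minor by type, so counts may be incomplete and not comparable

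*Protocol article*

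**What the plan says.** Under Adverse event reporting and harms {22}, the Protocol article names one expected event and labels it: "The minor adverse events that can happen are falls during physical exercise". It then says "If any happens, it will be immediately communicated and verified by the Data Monitoring Committee". For serious events it says that "if any serious adverse effects occur, they will be immediately reported and analyzed by the Data Monitoring Committee". Under Notification of intervention harm it gives the route by which harms become known: "Participants will have an online communication channel (telephone and email) to fill out a form highlighting adverse effects and harm", with a secretary passing the message to the committee.

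The Outcomes {12} section lists quality of life, pain, sleep, self-care agency, service use and costs, feasibility, adherence and a qualitative evaluation. It lists no harms item. Section {18b} repeats the primary and secondary variables after the intervention and at 3, 6 and 12 months.

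Staff contact is described separately for each arm:

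- **Experimental:** "Exercise sessions should be performed online with an approximate duration of 40 min each, once a week", and "Participants will be tended to online as a group and under the guidance of a physiotherapist". Section {11c} adds a call about absences, if needed. The intervention description also has participants instructed on weekly physical activity and "encouraged to perform them at home, in addition to what was proposed in the web-based program".
- **Control:** "once a week, the responsible physiotherapist will call each participant of this group to ask how the reading is going".

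**The concern.** Two features of the stated plan matter.

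First, a passive route records what people choose to volunteer. A participant who has a pain flare two days after a strengthening session, or who falls while exercising at home, has to decide that this counts as harm and then contact the study. In people with chronic widespread pain, a flare is easily taken as part of the condition. The text on immediate communication says what happens once an event is known. It does not say who asks.

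Second, calling falls minor grades by event type. A fall without consequence and a fall with injury carry the same advance label, and nothing in the section says what moves a fall into the serious category.

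At stake is the reading of a low count. The results are meant to inform future studies (Sample size {14}), and the authors plan to encourage use of the programme in primary care across Brazil (Dissemination plans {31a}). If few or no events are recorded, a reader could not tell a well-tolerated programme from one in which nobody was asked.

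**Working it through.** The article states no harm rate, reporting rate or power for harms, and its sample size rests on group size, not on a formula. There is no figure of its own to reproduce. The check has two parts.

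**1. Is there any scheduled point at which harms are asked about?**

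| Contact in the plan | Arm | Stated content |
|---|---|---|
| Weekly live group session | Experimental | Education and exercise led by staff |
| Call about absences, if needed | Experimental | Reason for absence |
| Weekly individual call | Control | Progress with reading, reminder |
| Monthly messages ({18b}) | Both | Positive messages to maintain the bond |
| Post, 3, 6 and 12 months | Both | Primary and secondary variables |
| Feasibility evaluation and interviews | Both groups for interviews | Experience, limitations, impact on life |
| Phone/email channel with form | Both | Adverse effects and harm, if the participant initiates |

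Only the last row concerns harms, and it is unsolicited. The form is nominally the same in both arms, but the surrounding contact is not. In one arm staff can see a fall during a session of about 40 minutes a week. In the other, a staff member speaks to each person alone every week.

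**2. How much could incomplete capture matter with 12 per arm?**

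Input from the article: n = 12 per arm (Sample size {14}). Assumed inputs: p, the true risk per participant of an event, and s, the share of affected participants whose event is reported.

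Chance of at least one recorded event in an arm = 1 − (1 − p·s)^12.

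| Assumed p | s = 100% | s = 50% | s = 25% |
|---|---|---|---|
| 10% | 1 − 0.90^12 = 72% | 1 − 0.95^12 = 46% | 1 − 0.975^12 = 26% |
| 20% | 1 − 0.80^12 = 93% | 1 − 0.90^12 = 72% | 1 − 0.95^12 = 46% |
| 30% | 1 − 0.70^12 = 99% | 1 − 0.85^12 = 86% | 1 − 0.925^12 = 61% |

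Expected numbers recorded at p = 20% are 12 × 0.20 × s = 2.4, 1.2 and 0.6 for the three shares.

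Apparent risk difference when the true risk is equal in both arms = p × (s_exp − s_ctrl). With p = 20% (assumed):

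- 90% reported in the experimental arm and 30% in the control arm: 0.20 × 0.60 = +12 points.
- 30% and 90%: −12 points.
- Equal shares: 0.

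The sign depends entirely on reporting shares that the article does not give.

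**The case against.** **The form is not said to be exclusive.** This stands. Sessions are live and led by a physiotherapist, who can see and report a fall, and the text on immediate communication does not exclude staff reports. A reader might infer that harms are recorded only through the form; the article does not say so. What can be said is that the form is the only route it describes. A steering group and an independent committee also review safety, but they can act only on what reaches them.

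**The minor label does not suppress a count.** This also stands. Any fall goes to the Data Monitoring Committee, and the serious-event paragraph does not exclude falls. The risk is wrong classification.

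**The direction of bias is unknown.** A reader might conclude that harms in the exercise arm will be under-counted. The document does not support that. Supervised sessions may make falls more visible in that arm, home events and delayed flares may be missed, and individual control calls may prompt reports in the other arm.

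**No harms comparison is planned, and 12 per arm could rarely support one.** Fair: five events against none are needed for a two-sided Fisher p below 0.05 (p = 0.037; four against none gives 0.093). Likewise, zero events in 12 leaves a one-sided 95% upper limit of 1 − 0.05^(1/12) = 22% even with full capture. That limit comes from the sample size, not from the capture method, and the fix would not change it. This argues for a descriptive table, not for leaving the question unasked.

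**A journal article leaves harms forms and grading to fuller documents.** This holds for a grading scale or case-report form, whose absence is not raised here. But the article does state a capture route and a severity label, and those stated choices can be improved.

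**Conclusion.** The point holds as a modest, inexpensive improvement. As written, harms capture relies on participants volunteering a form, no assessment carries a harms question, and falls are labelled minor before their outcome is known. Because routine contact differs by arm, counts may be incomplete and not comparable, and the direction of any distortion cannot be settled from the document.

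The size is illustrative only. With 12 per arm and half of events reported, both p and s being assumptions, the chance that an arm records no event at all is 54%, 28% and 14% for true risks of 10%, 20% and 30%. With full capture it is 28%, 7% and 1%.

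The document does not support the stronger conclusions that staff will not report events, that injurious falls will go uncounted, or that the exercise arm in particular will look safer than it is.

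**What to change.** 1. Ask one identical question in both arms, covering any new or worse symptom, fall or injury since the last contact. Put it in the existing weekly control call and the existing weekly experimental contact, and on each existing online assessment form. In the experimental arm let each person answer individually, for example with the weekly session link, so that answers do not depend on speaking up in a group and absentees are covered.
2. Record events seen by staff during sessions separately, since that source exists in one arm only.
3. Keep the spontaneous form as an addition.
4. Reword the sentence on falls so that severity and seriousness are classified by the outcome of the event, not by its type.
5. Tabulate events descriptively by arm and by source, without a significance test.

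Cost: one question added to contacts and forms that already exist, and a few more minor events to log. No new visits or staff are needed. One precaution applies: answers may reveal the arm, so they should not be shown to the blinded evaluator.

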#### Reporting of serious adverse events (SAEs)

Evidence suggests that SAEs are not expected, however, if any serious adverse effects occur, they will be immediately reported and analyzed by the Data Monitoring Committee.

#### Notification of intervention harm

In some situations, research may have unplanned or unforeseen harm or consequences, which may result in collateral damage or unwanted effects. If any of these happen, they will be immediately communicated and verified by the Data Monitoring Committee.

Participants will have an online communication channel (telephone and email) to fill out a form highlighting adverse effects and harm. A secretary will forward the message to the Data Monitoring Committee.

### Frequency and plans for auditing trial conduct {23}

#### Project management group

This is a specific team designated to plan, coordinate and supervise all activities related to the clinical trial. This group is essential to ensure that the trial is conducted properly, efficiently, and in compliance with established protocols and regulations for clinical research. The main responsibilities of the Project Management Group will include planning and organization, selection of centers and researchers, resource management, coordination and communication, monitoring progress, data management, risk management, and reporting and documentation. The joint work of the Project Management Group will be carried out by a group of 4 independent physiotherapists. Meetings will be online every 20 days.

#### Trial steering group

This group will represent a committee responsible for the supervision and general direction of the study. The main objective will be to provide an independent and unbiased review of the progress of the clinical trial, monitor the safety of participants, and review any issues or challenges that may arise during the development of the trial. The main responsibilities of this group will be as follows: general supervision of the study, regularly reviewing the progress of the study and its compliance with the research protocol; evaluation and approval of any relevant changes to the trial protocol, such as modifications to the inclusion/exclusion criteria or the method of data collection; ongoing monitoring of the ethical aspects of the study and ensuring that the study is being conducted in accordance with ethical principles and applicable regulations; participant safety assessment and review of any study-related adverse events; making important study-related decisions, such as continuation, modification, or early termination of the study; communicating with the research ethics committee and other regulatory authorities as needed; and finally, providing guidance and support to investigators and clinical trial staff. Membership of the Trial Steering Group will be carried out by a group of one (1) Physiotherapist, one (1) specialist in rheumatology, and one (1) patient with fibromyalgia. All three members will be independent. Meetings will be online every 20 days.

#### Independent data monitoring and ethics committee

This committee will play a crucial role in monitoring and overseeing the study. This committee will be independent because it operates separately from the research team conducting the study and the sponsors or interested parties involved. Its main objective is to protect the well-being and rights of study participants and to ensure the integrity and validity of research data. The main responsibilities of the Independent Data Monitoring and Ethics Committee include data monitoring, interim analysis, participant safety, ethical considerations, continuation or termination of the trial, and ultimately, the confidentiality and integrity of the data. This independent committee will be composed of 3 independent physiotherapists. Meetings will be online every 20 days.

